**Fig. 2 Fig2:**
[figure not shown]
Part 2 study design flowchart. For group details, see Table 2. d days, TEAS transcutaneous electrical acupoint stimulation

Anesthesia protocols will be identical in Part 1 and Part 2 of this study, with midazolam (0.03 mg/kg), propofol (1.5–2.5 mg/kg), sufentanil (0.3–0.4μg/kg), and rocuronium (0.8 mg/kg) used to achieve effective anesthesia, and with patients undergoing mechanical ventilation after tracheal intubation. Anesthesia maintenance during the intraoperative period will be achieved using remifentanil (0.05–0.2 μg/kg/min), propofol, and rocuronium. Sedation depth will be monitored according to the Bispectral Index (BIS), maintaining BIS values between 45 and 55 by adjusting the propofol infusion rate, and adjusting respiratory parameters to maintain a PetCO_2_ of 35-45 mmHg. If a patient’s heart rate (HR) falls below 50 bpm or to 30% below baseline, they will be given 0.25–0.5 mg atropine; if their HR rises to above 100 bpm or to more than 30% above baseline, esmolol (0.2–0.5 mg/kg) will be given as appropriate. If blood pressure falls to < 90/60 mmHg or to below 30% of baseline, 6 mg ephedrine will be administered to maintain hemodynamic stability. Sufentanil (5–10 μg) or 0.05 mg fentanyl will be given as appropriate following peritoneal suturing, and a prophylactic long-acting 5-HT_3_ receptor antagonist will be used. Patients will be connected with a PCIA pump (250 μg sufentanil plus saline to a total volume of 250 ml; 1 ml/h, 3 ml/bolus, 10-min interval). After skin suturing, sedative and analgesic drug administration will be terminated, and patients will be transferred to a post-anesthesia care unit (PACU). After patients resume spontaneous breathing, muscle relaxation antagonists (neostigmine 1–2 mg, atropine 0.5–1 mg, and flumazenil 0.5 mg, if necessary) will be given, and the extubation time will be recorded. Once the patient is fully awake, pain scores will be assessed and adverse events recorded.

GCP-trained nurses will check the bowel sounds by auscultation of the patients’ left lower abdomen or right lower abdomen at 3:00 a.m., 9:00 a.m., 3:00 p.m., and 9:00 p.m. each day on the 1st, 2nd, and 3rd postoperative days. Each auscultation will last for 3 min.

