### Outcome measurement

#### Primary outcome

The primary study outcome will be the time to first bowel sound recovery following surgery, defined as the first time point at which the bowel sounds are heard by GCP-trained nurses at three consecutive time points. The judgment of bowel sounds is based only on the results of auscultation by GCP-trained nurses, even if some patients may feel residual colon gas discharge early after surgery.

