### Statistical analysis

Continuous variables will be expressed as: mean (SD), median (interquartile range (IQR)), or minimum and maximum. For comparisons between treatment groups, analyses of variance (ANOVAs) will be used for normally distributed variables, and the Kruskal–Wallis *H* test will be used for non-normally distributed variables. Categorical variables will be expressed as numbers (%), and will be analyzed via chi-square tests for between-group comparisons.

Statistical significance for this study is defined as α = 0.05 for a two-sided test. *P* values will be rounded to three decimal places; values below 0.001 will be reported as < 0.001. Statistical analyses will be conducted using SAS version 9.4 (SAS Institute Inc.).

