### Missing data

Missing primary endpoint data will be imputed using the last-observation-carried-forward (LOCF) method. In cases of missing baseline data, the mean of all patients will be used for imputation. Missing data for other observations will not be imputed.

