### Primary/secondary efficacy endpoints

A covariance model (ANCOVA) will be fitted, with primary endpoint changes from baseline serving as the dependent parameter, and with treatment group, baseline, and study site serving as fixed effects for consideration of site–treatment interactions. For ordinal and categorical variables, a Cochran–Mantel–Haenszel (CMH) test will be used, with study site as a stratifying factor.

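### The only model named for the primary endpoint analyses a change from baseline that does not exist, and the plan does not say which test replaces it

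*Protocol article*

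**What the plan says.** The endpoint is defined under Primary outcome: "The primary study outcome will be the time to first bowel sound recovery following surgery". It is counted from the first of three consecutive auscultations at which bowel sounds are heard. According to the Interventions section (text after Fig. 2), nurses listen "at 3:00 a.m., 9:00 a.m., 3:00 p.m., and 9:00 p.m. each day on the 1st, 2nd, and 3rd postoperative days". No preoperative auscultation is scheduled.

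Under Primary/secondary efficacy endpoints, the article specifies an ANCOVA "with primary endpoint changes from baseline serving as the dependent parameter", "with treatment group, baseline, and study site serving as fixed effects for consideration of site–treatment interactions".

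The Missing data section adds: "In cases of missing baseline data, the mean of all patients will be used for imputation".

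The Statistical analysis section gives a general rule for comparing groups on continuous variables: "analyses of variance (ANOVAs) will be used for normally distributed variables", with Kruskal–Wallis for the rest. It also sets the significance level: "Statistical significance for this study is defined as α = 0.05 for a two-sided test". It does not mention study site and does not say whether the rule covers the primary endpoint.

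Under Sample size calculations, Part 1 is sized on a difference between mean recovery times in hours. Trial status reports that Part 1 has been analysed and that Part 2 is still recruiting.

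**The concern.** A duration that starts at surgery has no value before surgery. The ANCOVA needs two quantities, a change from baseline and a baseline, that neither exist nor are measured for this endpoint. This is a stated analysis that is wrong as written, not a detail left to another document.

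Two things are at stake. First, someone has to decide what replaces the model, and the candidates differ. The ANCOVA adjusts for study site and the general rule does not. ANOVA compares means, while Kruskal–Wallis compares ranks and gives no estimated difference in hours, the scale on which the trial was sized. Second, if the replacement is not fixed in advance, the primary p-value carries some freedom of choice, and the nominal 5% is then not assured.

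**Working it through.** **1. Can the stated model be fitted?**

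| Element | What the article gives |
|---|---|
| Outcome in the model | Change from baseline of the primary endpoint |
| Terms in the model | Treatment group, baseline, study site |
| Endpoint definition | One postoperative duration per patient |
| When it is assessed | Postoperative days 1 to 3, every 6 hours |
| Scale used for sizing | Raw hours: 60.320 − 51.558 = 8.762 h |

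There are two ways to try to rescue it:

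- *Treat baseline as missing.* No patient has an analysable record. Imputing the mean of all patients fails, because there is no observed baseline to average.
- *Set baseline to 0 for everyone.* The change score then equals the raw time and the baseline column is empty. For Part 1, with five hospitals as sites, the design matrix has 400 rows and 1 (intercept) + 3 (group) + 4 (site) + 1 (baseline) = 9 columns, but rank 8. The baseline effect cannot be estimated. What remains is treatment group plus site on raw hours, which is usable but is not the model described.

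**2. Which scale was the trial sized on?**

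Reproducing the plan's figure with a difference of 8.762 h, SD 17.8, two-sided 5%, power 90% and ratio 1.5:

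n (smaller arm) = (1 + 1/1.5) × [17.8 × (1.960 + 1.282) / 8.762]² = 72.27, rounded up to 73

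n (larger arm) = 1.5 × 73 = 109.5, rounded up to 110

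These are the stated 73 and 110. A one-sided test would give 59 and 89, so the two-sided formula was used. The calculation already uses raw hours, so analysing raw hours leaves it unchanged:

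- 73 vs 110: 8.762 / [17.8 × √(1/73 + 1/110)] = 3.261; power = Φ(3.261 − 1.960) = 0.903 (0.900 by the t-test)
- 80 vs 120: power 0.927
- 100 vs 100: power 0.936, assuming the same difference and SD hold in Part 2

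**3. What does an open choice of test cost?**

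This simulation is illustrative. It assumes no treatment effect, groups of 80/120/80/120, mean 56 h, SD 17.8, and 3,000 trials per setting. The plan names no normality check, so a Shapiro–Wilk test at 5% on group-centred values is assumed.

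| Data shape | ANOVA | Kruskal–Wallis | Chosen by normality test | Smaller of the two p-values |
|---|---|---|---|---|
| Normal | 0.051 | 0.050 | 0.051 | 0.062 |
| Lognormal | 0.049 | 0.054 | 0.054 | 0.065 |
| Rounded up to 6-hour grid | 0.047 | 0.048 | 0.049 | 0.061 |

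The simulation error is about √(0.05 × 0.95 / 3000) = 0.004. The written rule stays at the nominal level within that error. A free choice between the two tests adds about 1 to 1.5 percentage points.

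**The case against.** The strongest reply is that the intended analysis is visible. The trial is sized on raw hours, and with a time origin of zero the ANCOVA collapses to treatment group plus site. The section covers secondary endpoints too, some of which have preoperative values (SF-8, blood indexes), so template wording is a plausible source. A section specific to efficacy endpoints would normally take precedence over a general rule. A separate analysis plan may settle the matter. Data analysts are also blinded to allocation.

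Much of this stands, and it limits the consequences. It does not remove the error, because the sentence names the primary endpoint expressly. Precedence of the specific section would only point back to the model that cannot be fitted. A correct analysis plan would still contradict the published text. Blinding to group labels lowers the risk, but an overall p-value can be compared between tests without knowing the labels.

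A reader might infer more than the article supports:

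- *That the primary test is chosen after the data are seen.* Nothing says so. It is a possibility the text leaves open.
- *That no executable test exists.* ANOVA or Kruskal–Wallis can be run on raw hours.
- *That one confirmatory analysis of 800 patients fails.* Parts 1 and 2 are separate four-group comparisons of 400 patients each.
- *That the false-positive rate is 7 to 8%.* This requires reporting the smallest of three p-values (ANOVA, Kruskal–Wallis, site-adjusted model), which the article nowhere permits, and it depends on assumed hospital shares and between-hospital variance.
- *That the effect in hours would go unreported.* Descriptive summaries are planned whichever test is used. Only a model-based difference could be lacking.

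**Conclusion.** The point holds in a limited form. The only model named for the primary endpoint is undefined for every patient in both parts, and it does not match the raw-hours basis of the sample size. The article does not say whether the general rule takes its place, so on this document the primary test is open.

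The statistical cost is modest: about 5% if the general rule is applied as written, and about 6 to 6.5% if someone picks freely between its two tests. Those figures rest on the assumed mean, SD, distributions and normality test. They show what could happen, not what was done. How and when the Part 1 test was chosen cannot be determined from the article. Neither design nor sample size is affected, but the text needs correcting before Part 2 is analysed.

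**What to change.** Under Primary/secondary efficacy endpoints:

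- Make the outcome the raw time in hours from surgery to confirmed first bowel sounds, as defined under Primary outcome. For this endpoint, delete the change from baseline and the baseline term.
- Keep treatment group and study site. In Part 1, add surgical site (gastric or colorectal), the stratification factor given under Randomization and blinding.
- State that this model, not the distribution-dependent choice under Statistical analysis, is the primary test.
- Keep change-from-baseline wording only for variables with a preoperative value, namely SF-8 and the blood indexes.

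Apply this prospectively to Part 2, dated before its data are analysed. For Part 1, whose analysis is finished, report which model was used and when it was fixed. Label any re-analysis under the corrected model as post hoc.

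The cost is wording in the protocol and analysis plan plus a short disclosure for Part 1. No patients are added: 73 and 110 before drop-out, and the planned group sizes, stay as they are.

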##### Acupuncture-balanced anesthesia efficacy

Recorded variables for this outcome include: respiratory and circulatory function during and after operation, depth of anesthesia, dosage of anesthetics and analgesics during induction and intraoperative maintenance, respiratory recovery time after operation, anesthesia recovery time, extubation time, occurrence of restlessness, nausea and vomiting during the recovery period, and NRS pain scores after extubation.

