### Sample size calculations

This study utilizes a superiority design, and the sample size has been calculated according to the primary endpoint of time to first bowel sound recovery following surgery. Based on a single-center preliminary test, this recovery time was 60.320 ± 9.8167 h in sham TEAS-treated individuals and 51.558 ± 17.8499 h in patients who received TEAS during all phases of the perioperative period. Therefore, the difference between the two groups was 8.762 h. Adopting a conservative point of view, the larger standard deviation of 17.8 was used to calculate the optimal sample size. In Part 1, according to a ratio of 3:2 and a power of 90%, a total of 110 and 73 patients were needed per group. To additionally account for a 10% drop-out rate, these case numbers were increased to 120 and 80, respectively. The reason for this unbalanced design between the groups was that both the T1 and T3 groups underwent TEAS before and during the operation, and thus have the potential to achieve a better therapeutic outcome. To ensure maximal possible patient protection, 80 cases were included in the Con and T2 groups, while 120 cases were included in the T1 and T3 groups.

In Part 2, as all patients received the same preoperative and intraoperative interventions, the allocation ratio was altered to 1:1:1:1, with 100 participants per group.

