### Demographic characteristics, vital signs, and medical histories

Demographic characteristics, vital signs, and medical histories for all subjects will be summarized, and between-group comparisons will be conducted as outlined earlier.

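### In Part 2 the primary ANCOVA in effect adjusts only for study site; pre-specifying age, BMI and ASA grade could gain some precision at almost no cost

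*Protocol article*

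**What the plan says.** Under Primary/secondary efficacy endpoints, the protocol article specifies an ANCOVA with "treatment group, baseline, and study site serving as fixed effects" and mentions site-by-treatment interaction. The dependent variable is described as a change in the primary endpoint since baseline. No separate model is given for Part 2. The Statistical analysis section adds only unadjusted ANOVA, Kruskal–Wallis and chi-square comparisons.

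The primary outcome is the time to first bowel sounds after surgery, judged by auscultation (Primary outcome). Randomization is stratified by surgical site, gastric or colorectal (Randomization and blinding). Part 2 takes colorectal patients only (Interventions).

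On preoperative data, the article states: "Demographic characteristics, vital signs, and medical histories for all subjects will be summarized". Age, sex, BMI and past history are listed as collected (Safety analysis). ASA grade I–III is an inclusion criterion, so it is assessed for every patient. None of these variables is named as a term in any model.

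**The concern.** An ANCOVA gains precision from covariates that predict the outcome. The usual one is the outcome's own baseline value, and this endpoint has none, because a time counted from surgery does not exist before surgery. The baseline term therefore contributes nothing identifiable. The stratification factor cannot contribute in Part 2 either, since every patient there has the same value. What remains is study site.

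Precision matters more in Part 2 than in Part 1. Part 2 isolates the postoperative component of TEAS, and the Interventions section calls the postoperative effect seen in Part 1 slight. The planning difference of 8.762 h, by contrast, compares TEAS in all phases with sham TEAS in all phases. If the true Part 2 effect is smaller, a narrower interval is worth more.

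**Working it through.** **Inputs from the protocol article.**
- Test level (Statistical analysis): "Statistical significance for this study is defined as α = 0.05 for a two-sided test".
- Part 1 calculation (Sample size calculations): "according to a ratio of 3:2 and a power of 90" per cent; "the difference between the two groups was 8.762 h"; "the larger standard deviation of 17.8 was used".
- Drop-out 10%; stated evaluable numbers 110 and 73; Part 2 has 100 per arm at 1:1:1:1.

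**Assumed inputs.**
- 90 evaluable per arm in Part 2 (100 less the 10% used for Part 1).
- R², the share of the variance remaining after site that age, BMI and ASA grade explain: 0% to 20%. The documents give no figure for it.
- 17.8 h is taken as the SD remaining after site. It comes from a single-center preliminary test, so it contains no between-site variance, which makes this reasonable but still an assumption.

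**Step 1: reproduce the plan's own figure.** For the smaller group at 3:2,

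n = (1 + 1/1.5) × [(1.960 + 1.282) × 17.8 / 8.762]² = 72.3, rounded up to 73; the larger group is 1.5 × 73 = 109.5, rounded up to 110.

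This matches the stated 73 and 110. The same inputs at 1:1 give 87 per arm, and 87 / 0.90 = 96.7, rounded up to 97. The 100 per arm in Part 2 is in line with this.

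**Step 2: standard error of a Part 2 pairwise difference.**

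SE = 17.8 × √(2/90) × √(1 − R²)

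With R² = 0, SE = 17.8 × 0.1491 = 2.65 h. With R² = 0.20, SE = 2.653 × 0.894 = 2.37 h.

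**Step 3: power**, by the normal approximation Φ(difference/SE − 1.960). For 8.762 h with R² = 0: 8.762/2.653 − 1.960 = 1.34, so power is 91.0%. With R² = 0.20: 8.762/2.373 − 1.960 = 1.73, so power is 95.8%. The 4.381 h column is half the planning difference. It is an illustration only, since the protocol gives no figure for the postoperative effect.

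| R² (assumed) | SE (h) | 95% CI half-width (h) | Power at 8.762 h | Power at 4.381 h | Equivalent n per arm, 90/(1 − R²) |
|---|---|---|---|---|---|
| 0 | 2.65 | 5.20 | 91.0% | 37.9% | 90 |
| 0.05 | 2.59 | 5.07 | 92.3% | 39.5% | 94.7 |
| 0.10 | 2.52 | 4.93 | 93.6% | 41.3% | 100 |
| 0.20 | 2.37 | 4.65 | 95.8% | 45.5% | 112.5 |

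**Step 4: cost.** With 4 × 90 = 360 evaluable patients, four arms and up to five hospitals, a main-effects model has 360 − 1 − 3 − 4 = 352 residual degrees of freedom. Age (1), BMI (1) and ASA grade as three categories (2) leave 348.

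**The case against.** A model with treatment and site is valid as it stands. A condensed article may leave a covariate list to the analysis plan, which is not shown. That stands as a limit on the point: the current model does not make the result wrong. But the article does fix the terms of the primary model, and the one term that should carry prognostic information has no value for this endpoint.

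The baseline term might mean other baseline variables, since the Missing data section imputes missing baseline values. The wording leaves that open. However, the model sentence ties baseline to change in the primary endpoint, and no other variable is named. On either reading the covariates are not pre-specified.

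The gain may be negligible. This stands in full. No correlation between any covariate and bowel-sound time is given, entry criteria narrow the predictors (age 18–75 years, BMI 18–31, ASA I–III), and R² could be near zero. The normal-theory figures are also approximate. Auscultation is six-hourly and stops at 9 p.m. on day 3, so, with three consecutive positive checks required, the latest recordable time is 9 a.m. that day.

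A reader might go further and treat everything recorded up to the end of surgery as a covariate, "as all patients received the same preoperative and intraoperative interventions" in Part 2. The protocol does record "dosage of anesthetics and analgesics during induction and intraoperative maintenance". The documents do not support putting those doses in the primary model. Patients are randomized once enrolled and practitioners know the allocation (Randomization and blinding), so titrated doses are post-randomization values that knowledge of the arm could influence. A total opioid dose is also ill-defined: sufentanil and remifentanil cannot simply be added without conversion, and the anesthesia description allows fentanyl as an alternative at one step.

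**Conclusion.** The point holds as a minor, optional improvement to Part 2. As written, the primary model adjusts in effect only for study site, while preoperative variables that might predict recovery are already available. The possible loss is one of efficiency; nothing here suggests bias or an invalid test.

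The size depends wholly on the assumed R². Across 0% to 20% the standard error falls by between nothing and 11% (2.65 h to 2.37 h), and power at 8.762 h gains between nothing and about 5 points. This rests on 17.8 h being the SD after site and on 90 evaluable patients per arm. It would be wrong to infer that the protocol forfeits any particular amount of power.

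The point does not extend to Part 1. Trial status says that its recruitment and data analysis are finished, so nothing can be pre-specified there.

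**What to change.** Before Part 2 is unblinded, specify its primary model as follows:
- dependent variable: time to first bowel sounds itself, in place of a change from baseline;
- terms: treatment group, study site, age, BMI and ASA grade, all three covariates taken at their preoperative values;
- sensitivity analysis: the same model without age, BMI and ASA grade.

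Confirm that ASA grade is recorded in the case report form, since the article names it only as an entry criterion. Intraoperative opioid dose should stay out of the primary model. If it is wanted at all, use it in a sensitivity analysis with a defined conversion between opioids and its balance by arm shown.

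The cost is a change of wording and about four degrees of freedom out of some 350. No extra patients, visits or measurements are needed, and no clinical procedure changes.

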### Safety analysis

Safety analyses will be performed in subjects receiving at least one study intervention.

All adverse events will be recorded, and both the numbers of specific adverse events and subjects experiencing adverse events will be quantified as percentages.

All data will be managed by the Peking University Clinical Research Institute, which will be responsible for sample calculations, electronic randomization, data entry, checking, and statistical analyses. Personal information (including sex, age, ID number, BMI, telephone number, past history, etc.) about potential and enrolled participants will be collected in an anonymous way, and will never be leaked to any person or organization.

### Study monitoring

An independent data and safety monitoring committee (DMC) has been formed to monitor the safety of participants in this study. This DMC includes members with expertise clinical practices, statistics, and ethics. Safety reports that include all reported adverse events will be delivered to the DMC every 6 months in a blinded manner. The DMC will be able to recommend whether to stop or to modify the study protocol based on these safety reports. If the incidence of adverse reactions proves unacceptably higher than expected, the DMC has the ability to recommend suspending the study. The DMC can also suspend the study due to the occurrence of any unexpected or serious adverse events.

The first audit will be conducted within 1 week after the first patient enrollment in each research center. Routine follow-up audits will be performed 1–2 times/month, and the frequency of routine audits will be based on the enrollment speed at each center, or any obvious problems at each center (such as overt data abnormalities, program violations, or instances of serious adverse events). The last audit must be completed within 10 working days after the last patient completes follow-up. Auditing steps will include research center personnel training, CRF filling, verification of original data, quality control, screening for failed cases, serious adverse events, and program violations. This process will remain independent from the investigators and the study sponsor.

